#### Secondary outcomes

Further surgery for macular hole, performed or plannedBCVA using standard Snellen chart at 6 metresPatient-reported experience of positioning at 3 monthsPatient-reported health and quality of life as assessed at baseline and at 3 months using the National Eye Institute Visual Function Questionnaire (VFQ-25)

### End of study definition

The end of the study will be at the final assessment of the final subject.

## Statistical considerations

### Sample size and power calculation

Clinical consensus is that face-down positioning would be recommended if there were a difference of 15 % in success rates. This is the smallest clinically relevant treatment difference that we wish to detect. Previous studies [8] indicate that successful closure of large macular holes without advice to position face-down is 80 %. A study with 86 patients per group has 85 % power to detect a difference between 80 % in the face-forward positioning arm and 95 % in the face-down positioning arm. With a 10 % loss to follow-up, we are aiming to recruit 96 patients in each arm.

### Analysis

Baseline characteristics will be tabulated in the two treatment arms.

Proportions of macular hole closures at 3 months will be compared between treatment arms using logistic regression adjusting for age and sex, with site as a random effect.

Visual acuity at 3 months will be compared using linear regression adjusting for age, sex, and baseline visual acuity, with site as a random effect. We will also adjust for surgery type in the logistic regression analysis. Questionnaire scores assessed at 3 months will be compared using linear regression adjusting for age and sex, with site as a random effect.

The numbers of participants who decline to participate, fail screening, or withdraw or are lost to follow-up will be recorded in a Consolidated Standards of Reporting Trials (CONSORT) flow-chart.

The analyses will be on an intention-to-treat basis, and every effort will be made to collect complete data. If any outcome data are missing we will analyse available subjects only (this is unbiased under a missing-at-random assumption where missingness depends only on variables adjusted for in the analysis), but we will also perform secondary analyses investigating the missing-at-random assumption and involving further baseline covariates if necessary.

OCT scans will be anonymised and sent to two independent retinal surgeons who will grade the macular hole as closed; open and flat (without a cuff of subretinal fluid), or open and elevated (with a cuff of subretinal fluid). The readers will be masked to the identity and treatment allocation of the subject. In the event of any disparity in grading, a third independent retinal surgeon, also masked to identity and treatment allocation, will arbitrate.

A formal statistical analysis plan will be signed off by the Trial Steering Committee prior to analysis.

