### Rationale

The benefit of face-down positioning to the success of surgery is unproven; evidence to guide individuals on its impact is lacking and advice offered by clinicians varies widely. The current lack of evidence with which to guide patients has led to a lack of consensus among clinicians and wide variation in clinical practice.

To address the limitations in the evidence we will perform a trial to determine whether advice to position face-down, as opposed to face-forward, improves the probability of macular hole closure at 3 months after surgery, and so reduces the need for further surgery. We will test whether advice to position face-down results in a better outcome than an inactive face-forward position following surgery for large macular holes (≥400 μm).

A previous pilot randomised controlled trial (RCT) [7] has demonstrated the feasibility of this definitive RCT.

We have chosen to include only large macular holes (≥400 μm) because the available evidence suggests that face-down positioning is of more relevance to larger holes than for smaller macular holes [7–9]. In addition, the role of surgery in the management of smaller macular holes may be influenced in the future by the introduction of enzymatic vitreolysis techniques; intra-ocular injection of ocriplasmin can help induce closure in up to 40 % of smaller macular holes [10]. However, this approach is not designed for larger holes, the management of which is likely to involve surgery for the foreseeable future.

The proposed trial has been designed taking into account the views of individuals with macular holes and clinicians. The pilot study suggested a benefit of positioning following surgery for large macular holes. Previous pilot study subjects were invited to form a Patient Advisory Panel to advise on the design and methodology of this new RCT. Both patients and clinicians indicated that randomisation to either face-down positioning for as long as 10 days, or conversely to no positioning at all, would adversely affect recruitment to the trial because these alternatives are typically considered too arduous or would present too high a risk of non-closure, respectively. Instead, we have reached a consensus, based on the approach used by Guillaubey et al [8], on the alternatives of 5 days positioning either face-down or in an inactive face-forward position.

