### Randomisation

Eligible candidates will be invited to participate and to sign the consent form prior to surgery.

At the conclusion of standardised surgery across all sites, participants still eligible for inclusion will be allocated randomly 1:1 to one of the 2 treatment arms (refer to the flow diagram in Additional file 4) stratified by site, using random permuted blocks of size 4 or 6 in equal proportions.

Randomisation will be performed using a secure bespoke online randomisation service implemented by the PCTU (Pragmatic Clinical Trials Unit). Each site will be provided with a unique log-in username and password to access the service. Online randomisation will be available 24 hours a day, 7 days a week apart from short periods of scheduled maintenance. Access to the service will be restricted to staff as delegated by the Principal Investigator (PI). They will input the participant ID and details required for randomisation, and then will be presented with immediate on-screen randomisation. The randomisation system will have built-in checks to check that (1) the participant ID is not a duplicate, and (2) the date of birth is within the eligible age set in the protocol.

Once the subject has been randomised, the enrolment of this subject will be documented on the enrolment log. An Email will be automatically generated to notify the Chief Investigator’s (CIs) team and PCTU of all participants randomised to the trial.

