### Data collection

Table 1 shows the schedule of assessments.

**Table 1 Tab1:** Schedule of assessments

Assessment	Preoperative	Surgery	3 months postoperative
Age	x		
Sex	x		
Ethnicity	x		
Laterality	x		
Duration of symptoms	x		
BCVA	x		x
Lens status: phakic/pseudophakic	x		x
Informed consent	x		
Surgery		x	
Randomisation		x	
Macular hole diameter on OCT	x		
Macular hole status (closed; open flat; open elevated)			x
QoL VFQ-25 questionnaire	x		x
Subject-reported experience of positioning			x
If primary repair of macular hole failed, was second operation performed/planned			x

*BCVA* best-corrected visual acuity, *OCT* optical coherence tomography, *QoL* quality of life, *VFQ-25* Visual Functional Questionnaire

Pre-operative data collection:Demographic data (age, sex, ethnicity)LateralityDuration of symptomsBest-corrected visual acuity (BCVA) measured using Snellen charts at a standard distance of 6 metresOCT with recording of minimal hole diameter (see Additional file 5)

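### The primary closure model leaves out baseline macular hole diameter, forgoing a modest gain in precision and leaving a chance imbalance in hole size unadjusted

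*Protocol article*

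**What the plan says.** The Analysis section of the protocol article fixes the primary model: closure at 3 months "will be compared between treatment arms using logistic regression adjusting for age and sex, with site as a random effect". After the sentence on visual acuity it adds: "We will also adjust for surgery type in the logistic regression analysis". Closure is the only outcome in that section with a logistic model, so the primary covariates are age, sex and surgery type, with site as a random effect.

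Hole diameter has a prominent place elsewhere:

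- The schedule of assessments under Data collection lists "Macular hole diameter on OCT" as a preoperative item, and the Devices section defines how it is measured.
- The Inclusion criteria set a lower limit of 400 μm and no upper limit.
- The Rationale defends that limit because "the available evidence suggests that face-down positioning is of more relevance to larger holes than for smaller macular holes".
- Allocation is "stratified by site, using random permuted blocks of size 4 or 6 in equal proportions" (Randomisation), so site is the only stratification factor.

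Further baseline covariates are mentioned only for secondary analyses of missing data, if needed.

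**The concern.** The covariates are already chosen and published, so this is not a detail left open for the statistical analysis plan. Age and sex are in the model without a stated reason. The article mentions age only in connection with how often the condition occurs, and gives no link between sex and closure. Hole size is the characteristic on which the trial population was selected, and closure rates and the value of positioning are discussed in terms of it. The visual acuity model adjusts for baseline acuity, but the closure model has no comparable anatomical baseline.

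Two things are at stake. Adjusting for a prognostic baseline variable usually buys some power. And with few open holes expected, the single trial that is run may have arms that differ in hole size, with nothing in the primary estimate to allow for it. Adding diameter after the imbalance has been seen would look data-driven.

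**Working it through.** **1. The plan's own figure.** The Sample size section says that "successful closure of large macular holes without advice to position face-down is 80" per cent, takes "95 % in the face-down positioning arm", and states: "A study with 86 patients per group has 85 % power to detect a difference". Significance level and sidedness are not stated; I assume 5% two-sided, which reproduces the figure (one-sided would give 69).

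n = [1.960 × √(2 × 0.875 × 0.125) + 1.036 × √(0.80 × 0.20 + 0.95 × 0.05)]² / 0.15² = (0.917 + 0.472)² / 0.0225 ≈ 86 per arm.

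Power at 86 per arm is 85.1%, and 86 / 0.90 rounds up to 96. The stated power assumes no covariate adjustment.

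**2. Expected failures.** 86 × 0.20 + 86 × 0.05 = 17.2 + 4.3 = 21.5 open holes. With treatment, age, sex and surgery type at one parameter each, that is 21.5 / 4 = 5.4 failures per parameter. Adding diameter without removing anything gives 21.5 / 5 = 4.3.

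**3. Power with and without diameter.** The article gives no strength for the association between diameter and closure among holes of 400 μm or more, so a range is assumed. Simulation: 4,000 trials per scenario, 86 per arm, marginal closure held at 80% and 95%, standard-normal diameter, likelihood-ratio test. Age, sex, surgery type and site were not simulated. Simulation error is about 0.5 point.

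| Assumed odds ratio for non-closure per SD | Power without diameter | Power with diameter | Gain (points) |
|---|---|---|---|
| 1.0 | 88.4% | 88.7% | 0.3 |
| 1.5 | 88.1% | 88.8% | 0.7 |
| 2.0 | 87.9% | 89.9% | 2.0 |
| 3.0 | 87.9% | 91.7% | 3.8 |

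The levels exceed 85.1% because the likelihood-ratio test differs from the normal-approximation formula; the gain is the relevant comparison. A Wald-test version (2,500 trials per scenario, age and sex included) gave 84.6% to 86.0%, 84.2% to 87.1% and 85.3% to 88.6% at odds ratios of 2.0, 2.5 and 3.0, so gains of 1.4, 2.9 and 3.3 points.

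**4. Type I error.** In the likelihood-ratio simulation it was 5.1 to 5.7% without diameter and 5.2 to 5.9% with it.

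**5. Chance imbalance.** The standard error of the standardised mean difference in diameter is √(2/86) = 0.152. An absolute difference above 0.2 SD occurs in about 19% of trials, and above 0.3 SD in about 5%. At an assumed odds ratio of 2.5 per SD, these shift the closure difference by about 2 and 3 points. For scale, the standard error of that difference is √[(0.16 + 0.0475)/86] = 4.9 points, and the target difference is 15 points.

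**6. Power given an imbalance.** Simulation: 2,000 trials per scenario, age and sex against age and diameter, with larger holes in the face-down arm.

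| Odds ratio per SD | Imbalance | Age and sex | Age and diameter |
|---|---|---|---|
| 1.5 | 0.2 SD | 85.0% | 88.9% |
| 1.5 | 0.3 SD | 83.9% | 89.1% |
| 2.0 | 0.2 SD | 82.0% | 88.4% |
| 2.0 | 0.3 SD | 78.7% | 89.1% |
| 2.5 | 0.2 SD | 81.3% | 90.8% |
| 2.5 | 0.3 SD | 76.5% | 90.2% |

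An imbalance of more than 0.2 SD in this direction has a chance of about 19% / 2, or roughly 1 in 10. In the other direction the apparent effect is inflated.

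**The case against.** The strongest reply is that the protocol never says diameter predicts closure within its own population. The Rationale and Background say that positioning matters more for larger holes. That is effect modification across the large/small divide, not prognosis among holes already at or above 400 μm. This stands, and it is why the strength had to be assumed over a range that includes no association. Only a limited inference survives: if the effect of positioning depends on size, closure must depend on size in at least one arm. Whether that carries on above 400 μm is an assumption.

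Four stronger readings are tempting, and the document does not support them.

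- *The trial is underpowered without diameter.* The 85% is an unadjusted figure and is met. A possible gain is forgone; planned power is not lost.
- *Chance imbalance makes the comparison biased or invalid.* Under randomisation the type I error holds, and the interval already reflects such imbalance. A shift of 2 points is less than half of the 4.9-point standard error.
- *The covariate list contradicts itself.* The surgery-type sentence is awkwardly placed, but it can only refer to the closure model.
- *The missing-data statement fails without diameter.* Having diameter in the model would widen the conditions under which the available-case analysis is unbiased, but the same section already foresees secondary analyses with further baseline covariates.

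The objection that there are too few failures for another covariate also has force. It counts against adding diameter on top of the present list, not against exchanging it for sex.

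**Conclusion.** The point holds as a matter of efficiency and robustness; the plan is not in error. The primary model omits a measured variable that defines the population and is not balanced by design, while it includes one, sex, that the article does not connect with closure. On average the cost is about 0 to 4 points of power for assumed odds ratios of 1 to 3 per SD. In the roughly 1 in 10 trials where diameter is unbalanced by more than 0.2 SD against the face-down arm, the cost is larger: about 4 to 10 points at an imbalance of exactly 0.2 SD, for odds ratios of 1.5 to 2.5 (88.9 − 85.0 = 3.9; 90.8 − 81.3 = 9.5).

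These sizes rest on 86 evaluable patients per arm, closure of 80% and 95%, a 5% two-sided test, a normally distributed diameter with a log-linear effect, and an association whose strength the article does not give. The simulations left out site and surgery type. If diameter is unrelated to closure above 400 μm, there is essentially nothing to gain, but exchanging it for sex also costs essentially nothing.

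**What to change.** In the statistical analysis plan, before it is signed off and before outcome data are seen by arm, state one primary closure model in a single sentence: logistic regression with treatment, continuous OCT minimum hole diameter, surgery type and age as fixed terms, and site as a random effect. Diameter takes the place of sex, so there are still four fixed parameters (one each) and about 5.4 expected failures per parameter. Report the published model, with age, sex and surgery type, as a sensitivity analysis.

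The cost is a change to a published covariate list, which should be recorded with its reason, and one extra sensitivity analysis. No new data are needed, and the sample size does not change.

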For the primary outcome we have chosen successful closure of the macular hole because, according to our Patient Advisory Panel, this is directly relevant to patients; hole closure is essential for a favourable impact on sight and determines whether further surgery is required. Although visual acuity is a relevant measure of functional outcome, its validity is limited to some extent in the short term by the confounding influence of secondary lens opacity and does not directly determine the need for further surgery.

We have chosen not to attempt to measure objectively the compliance of subjects with positioning. This is because self-reported compliance is of unknown reliability, and objective monitoring risks influencing behaviour artificially and unpredictably. Instead, we have taken the pragmatic approach to determine the value of the *advice* to patients regarding position. However, following the period of positioning we will ask subjects to say retrospectively how easy they found it to maintain their allocated position (on a scale of 0 (very difficult) to 10 (very easy). We will also assess their quality of life using the National Eye Institute Visual Function Questionnaire (VFQ-25).

The trial will benefit patients by providing reliable information on the value of positioning following surgery for large macular holes, thereby enabling them to make an appropriately informed choice about the management of their condition.

The research will benefit the National Health Service (NHS) because by determining the value of face-down positioning we can expect to improve the likelihood of prompt successful surgery and hence reduce the amount of additional resource required for further clinical management and associated costs.

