### Exclusion criteria

Age-related macular degeneration; glaucoma; diabetic retinopathy; retinal degeneration; amblyopia; previous vitrectomy surgery (refractive error, lens opacity and previous use of ocriplasmin are not exclusion criteria).Traumatic macular hole.History of visual loss suggesting macular hole duration longer than 12 months.Presence of a retinal tear identified during surgery for which postoperative positioning is advised.

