## Informed consent

Eligible candidates will be approached at their baseline visit by the clinical team, provided with information about the trial and invited to participate. They will be given time to consider their decision and the opportunity to ask questions. Investigators will ensure that information about equipoise is provided impartially so as to avoid potential bias by influencing compliance with advice to position. Should candidates elect to participate, informed consent will be obtained (see Additional file 1) at the time of listing for surgery. Candidates will understand that that although consenting to participate in the trial, they will be formally enrolled only if the inclusion and exclusion criteria are still met following surgery.

We will not be recruiting/consenting subjects who we feel lack capacity.

The surgery will involve vitrectomy (using instruments of any gauge), internal limiting membrane (ILM) peeling (with or without staining by a vital dye), fluid-air exchange and injection of octafluoropropane (C3F8) 14 % gas. Vitrectomy may be combined with phacoemulsification and intra-ocular lens implant.

Subjects will be randomised immediately following surgery, unless exclusion criteria are met during surgery.

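### As printed, surgery type is adjusted for in the closure model but not in the visual acuity model, giving up some precision on an outcome that the protocol says lens opacity affects

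*Protocol article*

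**What the plan says.** The Analysis section of the protocol article lists covariates model by model.

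- Closure at 3 months: "logistic regression adjusting for age and sex, with site as a random effect".
- Acuity: "Visual acuity at 3 months will be compared using linear regression adjusting for age, sex, and baseline visual acuity, with site as a random effect".
- Directly after the acuity sentence: "We will also adjust for surgery type in the logistic regression analysis".

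No other logistic model is described, so read literally, surgery type enters the closure model only.

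Four other places bear on the point.

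- The Rationale says of visual acuity that "its validity is limited to some extent in the short term by the confounding influence of secondary lens opacity".
- The surgery description under Informed consent allows two forms of operation: "Vitrectomy may be combined with phacoemulsification and intra-ocular lens implant".
- The Exclusion criteria admit eyes with cataract: "refractive error, lens opacity and previous use of ocriplasmin are not exclusion criteria".
- Table 1 under Data collection has a row for "Lens status: phakic/pseudophakic", marked preoperatively and at 3 months. No model described uses it.

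On timing, the Informed consent section states: "Subjects will be randomised immediately following surgery, unless exclusion criteria are met during surgery". The Randomisation section stratifies by site and by nothing else.

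**The concern.** The trial enrols a mixture of eyes: already pseudophakic, phakic with the lens replaced at the macular hole operation, and phakic with the natural lens left in place. Only the last group can go on to develop opacity of the natural lens. In an eye that already has lens opacity, replacing the lens can change acuity whatever position is advised afterwards. Baseline acuity does not separate these groups, because it is measured before the lens is or is not removed.

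The protocol therefore names a lens-related limitation of acuity and then, as printed, applies the lens-related surgical covariate only to the other outcome. What is at stake is the precision of the acuity comparison and its protection against a chance imbalance in combined surgery between arms, which randomisation does not control beyond site.

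**Working it through.** **1. The plan's own figure.** The sample size section gives 86 per group for 85% power at 80% versus 95% closure, and 96 per arm after 10% loss. Assuming a two-sided 5% level (the article states none), the pooled-variance formula without continuity correction gives 86 per group, power at 86 is 0.851, and 86/(1 − 0.10) = 95.6, so 96. The figure reproduces and is not affected by this point. No power or SD is given for acuity.

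**2. Are the covariates admissible?** Randomisation takes place after the operation, so surgery type is fixed before allocation; so is preoperative lens status. Lens status at 3 months is measured after allocation and is not a baseline covariate.

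**3. Loss of precision.** Let q be the share of eyes with combined surgery and d the difference in 3-month acuity between surgery types, in units of the residual SD of the adjusted model. Both are assumed. Surgery type is read as vitrectomy alone versus vitrectomy combined with phacoemulsification, since the article does not define it. If it is unrelated to the other covariates, omitting it multiplies the residual variance by

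1 + q(1 − q)d²

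and the standard error by the square root of that. Take a difference that the adjusted model would detect with 80% power at 86 per arm, that is, 1.96 + 0.842 = 2.80 standard errors. Power without the covariate is then approximately Φ(2.80/√(1 + q(1 − q)d²) − 1.96).

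| q | d | Variance factor | SE increase | Power (80% if adjusted) |
|---|---|---|---|---|
| 0.2 | 0.25 | 1.010 | 0.5% | 79.6% |
| 0.2 | 0.5 | 1.040 | 2.0% | 78.4% |
| 0.2 | 1.0 | 1.160 | 7.7% | 73.9% |
| 0.3 | 0.5 | 1.052 | 2.6% | 78.0% |
| 0.3 | 1.0 | 1.210 | 10.0% | 72.1% |
| 0.5 | 0.5 | 1.062 | 3.1% | 77.6% |
| 0.5 | 1.0 | 1.250 | 11.8% | 70.7% |

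**4. Chance imbalance.** The SD of the between-arm difference in the share with combined surgery is √(2q(1 − q)/86): 0.061 at q = 0.2 and 0.076 at q = 0.5. A 10-point imbalance is therefore 0.10/0.061 = 1.6 to 0.10/0.076 = 1.3 SDs. It would shift the acuity difference by 0.10 × d, which is 0.025 to 0.10 residual SD for d from 0.25 to 1.0. The standard error of the adjusted comparison is √(2/86) = 0.152 residual SD, so the shift is roughly 0.16 to 0.66 of a standard error.

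**The case against.** **The sentence may be a slip.** It sits after the acuity model, not after the closure model. It may be misplaced, or the word logistic may stand where linear was meant. A reader might infer that the trialists deliberately left surgery type out of the acuity model; the text does not establish that. This objection stands as to intent. It does not remove the need for a change: either the acuity model lacks the covariate or the text names the wrong model.

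**The protocol's claim about lens opacity is mild.** A reader might take lens opacity to be the main threat to acuity. The Rationale says only that validity is limited to some extent in the short term, and says so in explaining why acuity is not the primary outcome. Nor is acuity the only window on sight, because the VFQ-25 also measures visual function.

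**There is no systematic bias.** A reader might infer that the acuity comparison is biased or its test invalid. Allocation is random, so a linear model without a prognostic baseline covariate still estimates the effect without systematic bias, and its wider standard error already reflects chance imbalance. The plan's missing-data argument, which relies on missingness depending only on adjusted variables, would be weakened if attendance depended on surgery or lens status, but nothing in the documents suggests that it does.

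**The size is assumed.** The documents give no acuity SD, no share of combined surgery and no effect of surgery type. Where surgery type follows site practice, site stratification and the site random effect absorb part of it, and the calculation above ignores this.

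**The remedy is partial.** Surgery type and preoperative lens status show which eyes can develop opacity, not which eyes do.

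**A formal analysis plan is promised.** It may settle the covariates. That lowers the consequence, but the article does state a covariate set for each model, and a better set is available from baseline information.

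**Conclusion.** The point holds as one about precision and clarity. As printed, the acuity model omits a covariate that the closure model includes, although the protocol itself gives a lens-related reason to expect it to matter for acuity, and although both surgery type and preoperative lens status precede randomisation.

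The loss is modest and falls on a secondary outcome. Under the assumed ranges, the standard error rises by about 0.5–12% and 80% power falls to between 79.6% and 70.7%; at a half-SD difference between surgery types, power is about 78%. These figures rest on assumed shares and differences and on surgery type being unrelated to the other covariates. They cover surgery type alone, not any further gain from preoperative lens status. The sample size of 96 per arm is untouched. Because the change is nearly free, it should be made.

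**What to change.** Before the statistical analysis plan is signed off:

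- State which model or models the surgery-type sentence refers to, and define surgery type (combined phacoemulsification or not).
- Add surgery type and preoperative lens status to the acuity model, for example as one three-level factor: phakic and left phakic; phakic with combined surgery; already pseudophakic. Keep age, sex, baseline acuity and the site random effect.
- State that lens status at 3 months will not be a covariate in this analysis, because it arises after randomisation.

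The cost is wording and two degrees of freedom in about 172 participants (2 × 86). Preoperative lens status is already in Table 1. Table 1 lists surgery without naming its type, but the planned adjustment for closure implies that type is recorded; confirm that the case report form captures it. The change reduces the lens problem for acuity only in part, since opacity that develops after surgery in phakic eyes remains.

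### The 3-month VFQ-25 comparison leaves out the baseline VFQ-25 score that the trial collects, losing precision and leaving chance baseline imbalance uncorrected

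*Protocol article*

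**What the plan says.** The Secondary outcomes section of the protocol article lists patient-reported "health and quality of life as assessed at baseline and at 3 months using the National Eye Institute Visual Function Questionnaire (VFQ-25"). In Table 1 (Data collection), the row "QoL VFQ-25 questionnaire" is marked both preoperatively and at 3 months. The baseline score will therefore be available.

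The Analysis section then fixes the model: "Questionnaire scores assessed at 3 months will be compared using linear regression adjusting for age and sex, with site as a random effect". Baseline VFQ-25 is not among the covariates. Earlier in the same paragraph the other continuous outcome with a baseline is handled differently: "Visual acuity at 3 months will be compared using linear regression adjusting for age, sex, and baseline visual acuity", again with a random site effect. No reason is given for the difference.

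Baseline covariates come up once more in that section, in "secondary analyses investigating the missing-at-random assumption and involving further baseline covariates if necessary". That provision concerns missing data and is conditional. It does not change the main VFQ-25 comparison.

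**The concern.** Quality of life is part of the trial's only secondary objective. If the baseline score predicts the 3-month score beyond what age, sex and site explain, leaving it out keeps that predictable between-patient variation in the error term. The standard error is then larger than it needs to be. The sample size was set for hole closure, so whatever precision the trial has for VFQ-25 is incidental and should not be given up.

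Randomisation is stratified by site only (Randomisation section), so the design does not balance baseline VFQ-25. If the arms happen to differ at baseline, part of that difference carries into the estimated effect: the baseline difference multiplied by the slope of the 3-month score on the baseline score.

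There is also a missing-data consequence. The Analysis section defends the available-case analysis on the condition that missingness depends only on covariates in the model. If patients with poor baseline scores are more likely to miss the 3-month questionnaire, a model with baseline VFQ-25 can meet that condition, but the planned model may not.

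**Working it through.** **Inputs from the protocol article.** The Sample size section states: "A study with 86 patients per group has 85 % power to detect a difference". The closure rates it assumes are 80% face-forward and 95% face-down. On attrition it says: "With a 10 % loss to follow-up, we are aiming to recruit 96 patients in each arm". No figure is given for VFQ-25, and no correlation between baseline and 3-month scores.

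**The plan's own figure.** Two-sided 5% is inferred here, because the section states neither the significance level nor the sidedness. With a pooled variance under the null and no continuity correction:

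- mean proportion = (0.80 + 0.95)/2 = 0.875
- n = [1.960 × √(2 × 0.875 × 0.125) + 1.036 × √(0.80 × 0.20 + 0.95 × 0.05)]² / 0.15² ≈ 86 per arm, with power 85.1% at 86
- 86/0.9 = 95.6, rounded up to 96 recruited per arm

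The stated size is reproduced, so 86 evaluable patients per arm is used below.

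**Assumption.** r is the correlation between baseline and 3-month VFQ-25 given age, sex and site, because those terms are already in the planned model. A marginal correlation would overstate the gain if age or site explains part of it. A range of 0.3 to 0.8 is shown. SDs are taken as equal at the two times.

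**Formulae.**

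- Variance factor from adding the baseline score: 1 − r². Standard error factor: √(1 − r²).
- Patients per arm the planned model would need for the same precision: 86/(1 − r²).
- Effect detectable with 80% power under the planned model: (1.960 + 0.842) × √(2/86) = 0.427 SD. With baseline in the model: 0.427 × √(1 − r²).
- Standard error of the chance difference between arms at baseline: √(2/86) = 0.152 SD. A difference of 1.96 standard errors is 0.30 SD. Left unadjusted, it moves the estimate by r × 0.30 SD.

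| Assumed r | Variance factor | SE factor | n per arm for same precision without baseline | Detectable effect with baseline (SD) | Power with baseline for an effect of 0.427 SD | Shift from a 1.96-SE imbalance if unadjusted (SD) |
|---|---|---|---|---|---|---|
| 0.3 | 0.91 | 0.954 | 95 | 0.408 | 84% | 0.09 |
| 0.5 | 0.75 | 0.866 | 115 | 0.370 | 90% | 0.15 |
| 0.6 | 0.64 | 0.800 | 134 | 0.342 | 94% | 0.18 |
| 0.7 | 0.51 | 0.714 | 169 | 0.305 | 97% | 0.21 |
| 0.8 | 0.36 | 0.600 | 239 | 0.256 | 99.7% | 0.24 |

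As a multiplier on sample size, 1/(1 − r²) is 1.10, 1.33, 1.56, 1.96 and 2.78 down the rows. One extra covariate costs one degree of freedom out of about 172 patients (2 × 86).

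**The case against.** The strongest reply is that this is a matter of efficiency, not validity. Allocation is randomised, so comparing 3-month scores without the baseline is unbiased over repeated randomisation and keeps its type I error rate. The ordinary standard error already allows for chance baseline imbalance on average. This stands: the omission does not make the quality-of-life result invalid.

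Second, the size of the loss is unknown. Surgery meant to change vision takes place between the two measurements, so the correlation could be modest. At r = 0.3 the standard error falls by only about 5% and power rises from 80% to about 84%. This also stands, and it is why the range starts there.

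Third, VFQ-25 is one of four secondary outcomes, and no power is claimed for it. That limits the importance of the point, but it does not justify setting aside data that are collected anyway.

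Fourth, the article is condensed and promises a formal statistical analysis plan, and its sentence covers questionnaire scores generically, so it may be shorthand. This carries less weight. The article is not silent: it names the covariates, and it does name the baseline for visual acuity. A statistical analysis plan that followed the text would carry the omission forward.

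**Conclusion.** The point holds. The protocol fixes a covariate list for the 3-month VFQ-25 score that omits a baseline it collects, and it treats visual acuity differently without explanation. The planned estimate is unbiased over randomisation but less precise than it could be, and it is open to a chance baseline difference.

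Over the central assumed range, r = 0.5 to 0.7, the variance is cut by 25% to 49%. At r = 0.3 the gain is small, at 9%. These sizes rest on the assumed partial correlation, 86 evaluable patients per arm and, for the imbalance figures, equal SDs at the two times. The omission itself rests on no assumption. The change should be made, but it concerns a secondary outcome and does not touch the primary analysis or the sample size.

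**What to change.** In the statistical analysis plan, before analysis, specify the VFQ-25 model as linear regression of the 3-month score on treatment arm, baseline VFQ-25 score, age and sex, with site as a random effect. This parallels the visual acuity model. The 0–10 rating of how easy positioning was has no baseline, so its model stays as planned.

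The plan should also say how a missing baseline score is handled, so that no patient with a 3-month score is dropped. One simple option is to replace it with the mean of all observed baseline scores, calculated without regard to arm.

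The cost is one covariate and one sentence in the plan. No new data, visits or patients are needed.
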